## Abstract

**Background:**

Inadequate fruit and vegetable consumption in childhood increases the risk of developing chronic disease. Despite this, a substantial proportion of children in developed nations, including Australia, do not consume sufficient quantities of fruits and vegetables. Parents are influential in the development of dietary habits of young children but often lack the necessary knowledge and skills to promote healthy eating in their children. The aim of this study is to assess the efficacy of a telephone-based intervention for parents to increase the fruit and vegetable consumption of their 3- to 5-year-old children.

**Methods/Design:**

The study, conducted in the Hunter region of New South Wales, Australia, employs a cluster randomised controlled trial design. Two hundred parents from 15 randomly selected preschools will be randomised to receive the intervention, which consists of print resources and four weekly 30-minute telephone support calls delivered by trained telephone interviewers. The calls will assist parents to increase the availability and accessibility of fruit and vegetables in the home, create supportive family eating routines and role-model fruit and vegetable consumption. A further two hundred parents will be randomly allocated to the control group and will receive printed nutrition information only. The primary outcome of the trial will be the change in the child's consumption of fruit and vegetables as measured by the fruit and vegetable subscale of the Children's Dietary Questionnaire. Pre-intervention and post-intervention parent surveys will be administered over the telephone. Baseline surveys will occur one to two weeks prior to intervention delivery, with follow-up data collection calls occurring two, six, 12 and 18 months following baseline data collection.

**Discussion:**

If effective, this telephone-based intervention may represent a promising public health strategy to increase fruit and vegetable consumption in childhood and reduce the risk of subsequent chronic disease.

**Trial registration:**

Australian Clinical Trials Registry ACTRN12609000820202

## Background

Inadequate fruit and vegetable consumption contributes to a variety of chronic diseases and is estimated to be responsible for 2.6 million deaths per year worldwide [1]. A substantial proportion of adults [2,3] and children [4] from developed countries, including Australia [5,6], consume insufficient quantities of fruit and vegetables. The 2002 World Health Report estimated that 4% of the disease burden in developed countries was attributable to low fruit and vegetable intake [7]. Increasing consumption in early childhood may be an effective strategy to reduce the risk of subsequent chronic disease associated with insufficient fruit and vegetable consumption, as dietary patterns in childhood appear to track into adulthood [8].

Parents are likely to be influential in the development of children's eating behaviours [9]. Parental practices associated with increased child consumption of fruit and vegetables include increasing the availability and accessibility of fruit and vegetables within the home [10], role-modelling fruit and vegetable consumption [11] and establishing family eating routines supportive of fruit and vegetable consumption, such as eating meals as a family [12] not in view of a television [13]. Despite such influence, a lack of knowledge and skills can prevent parents from utilising these opportunities to promote healthy eating habits in their children [14].

Assisting parents to create supportive home environments can be an effective strategy to increase the fruit and vegetable consumption of their children [15]. However, studies involving traditional means of delivering interventions to parents, such as education sessions, often report high drop-out rates [16] and low attendance due to barriers associated with transport, work schedules and lack of interest [17]. Parent participation in healthy eating interventions is also reportedly constrained by specific barriers associated with preschool-aged children, including unpredictable sleep times and frequent sickness [18]. Telephone-based interventions may overcome many of these barriers and provide a convenient and effective means for parents to receive healthy eating support for their children. For example, previous research with adults has found that telephone support is an acceptable method of delivering health information [19] and is an effective strategy in modifying a range of health behaviours, including smoking [20], physical activity [21] and diet [22-24]. Furthermore, almost all Australian households have telephones [25]; thus, telephone-delivered interventions have the capacity for broad reach, and may hold promise in specifically targeting disadvantaged communities [26].

Despite the potential of telephone-based interventions to provide effective and acceptable support to parents, the authors are not aware of any randomised controlled trials of such interventions specifically targeting healthy eating behaviours in preschool children. The study attempts to address this gap in evidence through the conduct of a cluster randomised controlled trial of a telephone-based parent-focused intervention to increase the fruit and vegetable consumption of children aged 3 to 5 years. This paper describes the methodology to be employed in the conduct of this trial.

## Methods/Design

### Study Aim

The aim of this study is to examine the efficacy of a four-week telephone-based parent intervention in increasing fruit and vegetable consumption of 3- to 5-year-old children, as assessed by parental report.

### Study Design

#### Overview of study design

The study employs a cluster randomised design, as outlined in Figure 1. The research will be reported in accordance with the requirements of the CONSORT statement [27]. Parents of 3- to 5-year-old children attending randomly selected preschools in the Hunter region of New South Wales, Australia, are being approached to participate. Preschools will be randomised to either control or intervention groups using a random number function in Microsoft Excel. Parents of children attending preschools allocated to the intervention group will receive a series of instructional resources and four 30-minute telephone calls delivered weekly by trained telephone interviewers. Parents of children attending preschools allocated to the control group will receive a readily available nutrition resource published by the Australian Government [28]. To assess the efficacy of the intervention, surveys will be conducted with parents *via *Computer Assisted Telephone Interview (CATI) at baseline (occurring one to two weeks prior to commencement of intervention delivery) and two, six, 12 and 18 months following baseline data collection.

### Research Setting

The study region encompasses non-metropolitan 'major cities' and 'inner regional' areas as described by the Australian Standard Geographic Classification system [29]. The region has lower indices of socio-economic status than the national average and has 485,700 residents, with 18,200 children aged 3 to 5 years [29]. Nine percent of Hunter residents speak languages other than English [30].

### Participants and Research Eligibility

#### Preschools

Thirty preschools will be recruited into the trial. Preschools in Australia provide educational and developmental programs for children (3 to 5 years) for up to two years prior to the commencement of full-time primary school education [31]. Preschool services are usually provided by qualified teachers for approximately six hours per weekday [32]. Sixty-four percent of all 4-year-old children in New South Wales attend preschool, with an average attendance of 17 hours per week [33]. Each preschool in the study area provides, on average, care for 27 children per day [34].

A current list of all preschools in the region that are licensed to provide care for 3- to 5-year-old children will be obtained from the New South Wales Department of Community Services (the licensing agency). Preschools will be excluded from the trial if they provide meals to children in their care (as this limits parents' capacity to influence the foods their children consume), cater exclusively for children with special needs (given the specialist care required for such children), are Government preschools (as conduct of the research has not been approved by the New South Wales Government Department of Education and Training) or have participated in child healthy eating research projects within six months of the commencement of recruitment. Information regarding eligibility of preschool services will be confirmed by preschool supervisors during phone contact as part of the recruitment process.

#### Parents

Four hundred parents will be recruited to the study. To be eligible, each participant must be a parent of a child aged 3 to 5 years attending a participating preschool, must reside with that child for at least four days a week (in order for the child to be sufficiently exposed to the intervention strategies that the parent may implement), must have some responsibility for providing meals and snacks to that child, and must be able to understand spoken and written English. Information regarding parent eligibility will be ascertained from completed study consent forms and verified during phone contact with parents immediately prior to baseline data collection. Parents will be excluded from the trial if their children have special dietary requirements or allergies that would necessitate specialised tailoring of the intervention or that may be adversely affected by the intervention. Such exclusions will be determined by an Accredited Practising Dietitian who is independent of the research team.

### Recruitment and Allocation

#### Preschools

Prior to formal requests to participate, the research trial will be promoted to preschools within the region through existing networks established by the *Good for Kids. Good for Life *program, a high-profile childhood obesity prevention program in the region [35]. Agreement has been reached with the *Good for Kids *program for this research project to utilise the *Good for Kids *brand and the program's communication channels with preschools. Specifically, newsletters and program emails will be used to make preschool supervisors aware of the trial and of what will be required of them if they consent to participate.

Participating preschools and the order in which they are to be approached to participate will be randomly selected from the New South Wales Department of Community Services database by an independent statistician using a random number function in Microsoft Excel. Recruitment will be staggered over a four- to five-month period due to intervention delivery capacity constraints. Preschools will therefore be approached in batches, until the desired sample of parents is achieved. The supervisors of the selected preschools will be sent letters and consent forms informing them of the study and requesting permission to recruit parents through their services. Consent will be obtained when the supervisor faxes or posts the consent form back to the research team. Two weeks after the initial information letters are sent to supervisors, a study research assistant will telephone supervisors who have not yet returned their consent forms to answer any questions they may have and to remind them to return their forms, confirming their consent or otherwise. Similar recruitment methods employed by the researchers as part of an Australian healthy eating and physical activity study were successful in achieving a childcare service participation rate of 84% [34].

#### Parents

In order to maximise parent participation in the study, a recruitment strategy based on a review of successful recruitment practices within the school setting [36] has been devised. Recruitment will incorporate the following four strategies recommended to maximise research participation.

##### 1. Recruitment oversight

One member of the research team will act as a dedicated recruitment coordinator. All preschool supervisors and parents will be provided with the direct phone number of the coordinator for all enquiries regarding research participation. The coordinator will also manage the rate at which preschools are recruited and monitor preschool and parent consent form return rates. The recruitment coordinator will not be involved in the delivery of the telephone support or the collection of data.

##### 2. Promotion of the research prior to requests for participation

A promotional flyer explaining the study will be sent to supervisors to disseminate to all parents at consenting preschools. The flyer will inform parents of the trial and the opportunity to participate, and will include endorsement of the research by a clinical psychologist and parenting expert. Such contact prior to a formal request to participate has been shown to increase response rates to postal questionnaires [37] and will be important in engaging parents where face-to-face contact is not possible. The project name, flyer and recruitment documentation will include the *Good for Kid*s logo and brand name [35]. Following a recent media campaign, unpublished data indicated that 59% of parents within the area reported that they were aware of the *Good for Kids *program.

##### 3. Dissemination of recruitment materials via methods to maximise parent engagement

The recruitment coordinator will arrange for recruitment packs to be delivered to each participating preschool, enough for one per family of each enrolled child aged 3 to 5 years. Distribution of these packs to parents will occur *via *methods considered by the preschool supervisor to be most effective and appropriate in engaging parents. Where possible, research staff will attend the preschool, hand out recruitment packs to parents and be available to answer parent questions. The recruitment pack consists of an information sheet, a consent form and a return envelope. The pack is brightly coloured and specifies that the study is being conducted in conjunction with a university; these strategies are suggested to increase response rates among those parents who have only received written communication during recruitment [37].

##### 4. Parent reminders

One to two weeks after delivery of the recruitment packs, reminder letters will be disseminated to parents, reminding them of the study and the opportunity to participate.

Parents will be asked to return the consent forms in the envelopes provided and place them in drop-boxes at their children's preschools within three weeks. The consent form includes a brief set of questions to establish the child's usual fruit and vegetable consumption. In order to identify any bias due to selective non-participation, all parents of 3- to 5-year-old children will be encouraged to complete the items on the consent forms and return them, regardless of whether they choose to participate.

#### Random allocation of preschools

Following the recruitment of parents within a preschool, an independent statistician will randomly allocate the preschool to an intervention or a control group using a randomisation function in Microsoft Excel. Randomisation at the unit of the preschool, rather than the individual parent, will reduce the potential for intervention contamination between parents whose children attend the same preschool [38]. Based on evidence suggesting that children's eating environments differ by socio-economic status [39], the randomised allocation will be stratified by the socio-economic status of the area in which the preschool is located [40]. Preschools with a postcode in the top 50% of the state, based on Socio-Economic Indexes for Areas (SEIFA) [41] will be defined as 'high socio-economic area preschools' and those within the lower 50% will be defined as 'low socio-economic area preschools'. Preschools will be randomised in a 1:1 (intervention:control) ratio in randomly sequenced blocks of between two and six preschools. Block randomisation will maximise the likelihood that the number of participants allocated to each group remains approximately equal [42]. Due to the difficulty in concealing group allocation from participants, parents will not be blinded, and following baseline data collection they will receive letters informing them that they will receive either print materials or telephone support.

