#### Sample size

A sample size of approximately 300 participants (150 per group) at the 18-month follow-up will allow a detectable difference between intervention and control groups of 1.27 on the fruit and vegetable subscale of the Children's Dietary Questionnaire, with 80% power at the 0.05 significance level. This sample size accounts for the effect of clustering by assuming an interclass correlation coefficient of 0.03 (unpublished data from the *Good for Kids *program) and assumes 10 participants per preschool remain at the 18-month follow-up (as explained below).

Four hundred participants will be required to be recruited at baseline to achieve the desired sample of 300 at the 18 month follow-up. Based on preschools caring for an average of 27 children each day [34], and assuming children attend preschool for an average of 2.8 days per week (i.e. 17 hours over 6-hour long days), it is expected that up to 48 parents of children, on average, will be eligible to participate in the trial from each consenting preschool. A parent participation rate of 30% [19] will yield approximately 14 parents per preschool at baseline, of whom 10 will remain at 18 months, assuming a 25% attrition rate [63]. It is thus estimated that 30 preschools will be required to generate a sample of 300 parents at the conclusion of the trial.

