#### Statistical analysis: primary outcome

All statistical analyses will be performed with SAS (version 9.2 or later) statistical software.

To assess the initial impact of the intervention and the extent to which any intervention effect is maintained in the longer term, the primary outcome analyses for the trial will be conducted on participant scores on the fruit and vegetable subscale of the Children's Dietary Questionnaire collected at the two-month and 18-month follow-up time periods. For the primary outcome analyses, an alpha value of 0.05 will be utilised to determine statistical significance.

Outcome data will be analysed using general estimating equations based on the intention-to-treat principle, where participants are analysed based on the groups to which they were allocated, regardless of the treatment type or exposure that they actually received [64]. General estimating equation models will account for any clustering effect of preschools. To ensure the results of the primary analysis are robust against the missing data assumption of the general estimating equation, a sensitivity analysis will be performed whereby participants' observations at baseline will be used as a substitute for subsequent missing data. A per-protocol analysis will also be conducted whereby outcome data will only be included in analyses if participants received and completed all four telephone support calls. Conducting both intention-to-treat and per-protocol analyses is recommended when assessing trial outcomes [64].

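### Allocation is stratified by area socio-economic status, but the primary GEE as described names only preschool clustering; fitted that way, its standard errors may be moderately too large

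*Protocol article*

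**What the plan says.** The section on random allocation of preschools gives a reason for stratifying, "Based on evidence suggesting that children's eating environments differ by socio-economic status", and then the rule: "the randomised allocation will be stratified by the socio-economic status of the area in which the preschool is located". The stratum has two levels, set by whether the preschool's postcode falls in the upper or lower half of the state on SEIFA. Within that scheme, "Preschools will be randomised in a 1:1 (intervention:control) ratio in randomly sequenced blocks of between two and six preschools".

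The section on the statistical analysis of the primary outcome says "Outcome data will be analysed using general estimating equations based on the intention-to-treat principle". On how the model reflects the design it says only this: "General estimating equation models will account for any clustering effect of preschools". It also gives the software, the two primary time points, the alpha level, a sensitivity analysis for missing data and a per-protocol analysis. It does not mention the stratum. It lists no covariates and does not call the model unadjusted.

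The sample size section sets the scale. "A sample size of approximately 300 participants (150 per group) at the 18-month follow-up" is said to allow "a detectable difference between intervention and control groups of 1.27" on the fruit and vegetable subscale, "with 80% power at the 0.05 significance level". The allowance is for clustering alone, with no credit taken for stratification.

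**The concern.** The randomisation has two structural features, clusters and strata, and the description of the model takes up only the first. Blocked allocation within strata keeps the arms alike in socio-economic mix, so differences between high and low areas contribute little to the true sampling error of the treatment contrast. A model without the stratum still places those differences in the residual between-preschool variance and estimates the standard error from it.

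Intervals are then wider than the design warrants and the test rejects less often than its nominal level. What is at stake is precision in a trial of 30 preschools, not validity. The article's own reason for stratifying presumes that the factor is related to what children eat, so a loss is plausible, though the article gives no figure for its size.

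**Working it through.** **Inputs from the article.** ICC 0.03; 10 participants per preschool at 18 months; 150 per group; 30 preschools; detectable difference 1.27; 80% power; alpha 0.05.

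**Assumptions.** Two-sided test; equal preschool sizes; strata exactly balanced by arm; the ICC of 0.03 includes any socio-economic component. The share *s* of between-preschool variance explained by the stratum is not given, so the whole range 0 to 1 is shown. The figures apply to the 18-month time point, the only one that the sample size section covers.

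**The plan's own figure.** Design effect = 1 + (10 − 1) × 0.03 = 1.27, which happens to be the same number as the detectable difference. No outcome SD is given, so 150 per group cannot be reproduced independently. Working backwards, the nominal SE is 1.27 / (1.960 + 0.842) = 0.453, and SD = 0.453 / √(2 × 1.27 / 150) ≈ 3.48. The baseline number does reproduce: 300 / (1 − 0.25) = 400.

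**Effect of leaving the stratum out.** In units of SD²/10, the variance of a preschool mean is 0.97 + 10 × 0.03 = 1.27 with the stratum ignored, and v(s) = 0.97 + 10 × 0.03 × (1 − s) once it is removed.

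- SE ratio (estimated to true) without the stratum: r = √(1.27 / v(s)).
- True alpha without the stratum: 2 × [1 − Φ(1.96 r)].
- True SE under stratified allocation: 0.453 / r.
- Detectable difference without the stratum: 1.96 × 0.453 + 0.842 × 0.453 / r, because the critical value uses the inflated SE while the estimate varies with the true one.
- Detectable difference with the stratum: 2.802 × 0.453 / r.

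| s | v(s) | r | true alpha, without | detectable difference, without → with | power at 1.27, without → with |
|---|---|---|---|---|---|
| 0 | 1.270 | 1.000 | 0.050 | 1.27 → 1.27 | 80.0 → 80.0% |
| 0.25 | 1.195 | 1.031 | 0.043 | 1.26 → 1.23 | 80.7 → 82.3% |
| 0.5 | 1.120 | 1.065 | 0.037 | 1.25 → 1.19 | 81.5 → 84.7% |
| 0.75 | 1.045 | 1.102 | 0.031 | 1.23 → 1.15 | 82.3 → 87.0% |
| 1 | 0.970 | 1.144 | 0.025 | 1.22 → 1.11 | 83.2 → 89.4% |

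None of these columns needs a separate SD value: r and alpha depend only on the ICC and preschool size, and the rest scale from the stated 1.27.

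To give *s* a meaning on the scale, the gap between two equal strata is 2 × √(0.03 s) × 3.48: about 0.85 points at s = 0.5 and 1.21 at s = 1, on a subscale that runs from 0 to 28.

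**Simulation.** Thirty equal preschools were split 16 and 14 by stratum and balanced by arm, with 40,000 runs per scenario and a t test on preschool means. Alpha without the stratum was 0.051, 0.037 and 0.024 for s = 0, 0.5 and 1. With it, alpha was 0.051, 0.050 and 0.050. Power was 77.0, 78.2 and 79.4% without, against 76.9, 82.0 and 87.2% with. Power starts near 77% rather than 80% because the SD was back-solved from the normal approximation while the test used t.

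An uncorrected robust z test in the same runs gave alpha of 0.070, 0.053 and 0.037 without the stratum and 0.074 to 0.075 with it. With few clusters that test is liberal whether or not the stratum is included. The conservatism described here is therefore relative to whatever level the chosen standard error would otherwise deliver.

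**The case against.** The strongest reply is that the article is silent, not wrong. A reader might infer that the stratum has been deliberately left out of the primary model. The text does not support that. It is a condensed methods paragraph with no covariate list, it never says the model is unadjusted, and such a list commonly sits in a full protocol or SAP that is not shown. The two sections do not contradict each other. This stands, and it limits the point to what follows if the model is fitted as described. It does not remove the point, because the stratum belongs to the randomisation that the article itself describes and justifies, and the analysis section does say how the model reflects the design, for clustering only.

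The second reply is that the size is unknown. A reader might take the loss of precision as certain, since the authors stratified for a prognostic reason. But the cited reason concerns eating environments and gives no figure for the outcome score, and a two-level postcode split is a coarse marker. At s = 0 nothing is lost. This also stands.

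Third, a reader might credit the stratum term with the whole fall from 1.27 to 1.19, or to 1.11. That overstates it. Stratified allocation has already lowered the true standard error, so the right starting points are about 1.25 and 1.22. The baseline score, collected with the same survey, may also carry part of any stable socio-economic difference, leaving less for the stratum to explain if the model adjusts for it.

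Finally, the error is in the safe direction. A reader might infer that the primary test is invalid or the trial underpowered. Neither follows: leaving the stratum out does not bias the estimate or raise alpha, and power at 1.27 is no lower than it would be if the stratum had no predictive value.

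**Conclusion.** The point holds as a minor, conditional one. If the primary GEE is fitted with preschool clustering and no stratum term, its standard error is too large by 0 to 14% and its true two-sided alpha is 0.050 down to 0.025, depending on a share that the article does not give. At an assumed share of one half, the overstatement is 6.5%, alpha is 0.037, and the forgone gain is about 0.05 to 0.06 points in detectable difference, or 3 points of power. The most that could be forgone, at a share of 1, is about 6 points of power. The ICC of 0.03 caps the effect, because the stratum can explain no more than the 3% of variance that lies between preschools.

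The result rests on the assumptions listed with the working. Incomplete blocks would leave the strata only approximately balanced and reduce the effect somewhat.

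**What to change.** Add one sentence to the section on statistical analysis of the primary outcome, stating that the high/low SEIFA stratum used for allocation enters the primary GEE, and its sensitivity analyses, as a fixed effect. If a full protocol or SAP already says so, a cross-reference is enough.

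The cost is one cluster-level degree of freedom out of 30 preschools. In the simulation this was negligible when the stratum had no effect (power 76.9% against 77.0%). No new data are needed, since the stratum is fixed at allocation, and the sample size need not change, since it claims no gain from stratification.
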